#### 2.6.1. Active NBO (Study Group)

Patients will be exposed to NBO conditions in Study Group 1 (aNBO), including oxygen levels of 32–40% (compared with about 21% in the atmosphere), pressure maintained at 1500 hPa (compared with about 1000 hPa outside), carbon dioxide levels between 0.7 and 1.9% (compared with 0.03% in the atmosphere), and hydrogen levels between 0.5 and 1% (which is 10,000 to 20,000 times higher than in the atmosphere). The exposure time in the NBO chamber will be the standard 2 h with an additional 20 min for preparation and adaptation and 10 min for finalization and the decompression period.

#### 2.6.2. Placebo NBO (Control Group)

Patients will be exposed to atmospheric conditions in the same NBO chamber (without normobaric conditions to provide a sham-placebo intervention) in Control Group 2 (pNBO), including oxygen levels at about 21%, pressure maintained at about 1000 hPa, carbon dioxide levels at about 0.03%, and hydrogen levels at about 0.00005% (0.5 parts per million, like in the atmosphere). The primary comparator in this study is the placebo NBO group (n = 127) for CRC patients, which serves to differentiate the specific effects of active NBO from the natural course of treatment without enhanced oxygen exposure.

### 2.7. Research Plan

The patient assessment scheme contains six visits from V0 to V5 with subsequent analytical packages with a detailed explanation provided in Section 2.8. The patient assessment schedule consists of six visits, from V0 to V5, each including specific evaluations and interventions. The study will begin with V0 (prequalification/screening), where patient consent will be obtained, medical history will be collected, and baseline data will be recorded. V1 (randomization and pre-test visit) will involve the initial assessments, including anemia, stress, immune function, genetic markers, and patient-reported outcomes (PROMs). Following this, the first phase of the NBO intervention (sessions 1–5) will take place over five weeks. At V2 (midpoint evaluation), the same set of assessments will be repeated to track progress, followed by the second phase of the NBO intervention (sessions 6–10) conducted over the next five weeks. V3 (finalization and post-test visit) will mark the completion of the intervention, with a final round of primary and secondary outcome assessments. The study will then proceed with two follow-up visits: V4 (3 months post-NBO) and V5 (6 months post-NBO), where anemia, stress, immune function, genetic markers, and PROMs will be reassessed to evaluate the long-term effects of the intervention. Table 1 presents the research plan (Figure 1).

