For the CRC groups (Groups 1 and 2), it was determined that 127 patients per group are required. This accounts for a potential 30% dropout rate, ensuring that the final sample maintains the desired power and accounting for the challenges associated with patient retention over the study period. The sample size calculations were performed using G*Power software (version 3.1.9.7 or the latest version). The parameters used in the calculation included the expected effect size (d), calculated based on the anticipated difference and standard deviation from pilot studies or the existing literature. An allocation ratio (N2/N1) of 1 was used, indicating equal allocation between the active NBO and placebo groups. The test family selected was *t*-tests for means between two independent groups, focusing on the difference between two independent means.

Assumptions made during the calculation included a confidence level of 95% and the use of a two-tailed test, considering the possibility of the effect in both directions. It was also assumed that the variability in outcome measures would be similar across groups, which is important for the validity of the statistical tests used.

The rationale for this sample size is to ensure that the study is sufficiently powered to detect clinically meaningful differences between the active NBO and placebo groups in the primary outcome measures. By accounting for a 30% dropout rate, the study design acknowledges the realities of clinical research involving patients undergoing chemotherapy, who may experience side effects or other factors leading to withdrawal from the study.

An interim analysis will be conducted after 50% of participants have completed the study. The research team will assess data on safety and efficacy trends during this analysis. Based on interim findings, sample size adjustments may be considered, adhering to statistical guidelines to control for Type I error inflation and ensuring the integrity of the study.

Statistical analyses will be performed using software such as SPSS (version 26 or later) and R (version 4.0 or later) with appropriate packages. Supplemental tools like SAS 9.4 M8 or Stata 19 may be used if needed. Data management will involve entering data into a secure database with validation checks to ensure accuracy. Data cleaning procedures will be implemented prior to analysis to address any inconsistencies or errors.

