Handling of missing data is an important aspect of the analysis plan. An intention-to-treat (ITT) analysis will be conducted, including all randomized patients in the analysis according to their assigned groups. Missing data will be handled using appropriate statistical methods such as multiple imputation or last observation carried forward (LOCF), depending on the nature and extent of the missing data. Additionally, a per-protocol (PP) analysis will be conducted as a secondary analysis, including only patients who completed the study without major protocol deviations, to assess the robustness of the findings.

Adjustment for multiple comparisons will involve the use of Bonferroni correction or other suitable methods when conducting multiple statistical tests. This approach helps control the overall Type I error rate, reducing the likelihood of false-positive findings due to multiple tests. Sensitivity analyses will also be performed to assess the robustness of the results under different assumptions and statistical models, providing additional confidence in the study conclusions.

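### V3 is tied to finishing the NBO course, and V4 and V5 to the end of NBO, not to fixed weeks from randomization, although the analysis is ITT and by visit label

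*Protocol article*

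**What the plan says.** V1 is time zero: "V1 (randomization and pre-test visit) will involve the initial assessments". Two session blocks follow. In the first, "the first phase of the NBO intervention (sessions 1–5) will take place over five weeks", and V2 comes next. The text then has V2 "followed by the second phase of the NBO intervention (sessions 6–10) conducted over the next five weeks". Table 1 repeats the two five-week blocks. Of the post-test, section 2.7 says that "V3 (finalization and post-test visit) will mark the completion of the intervention". The follow-up visits are dated from the end of treatment: "The study will then proceed with two follow-up visits: V4 (3 months post-NBO) and V5 (6 months post-NBO").

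Section 2.6 gives a different course length: ten sessions in five weeks, at two per week.

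The analysis in section 2.10 runs over the visit labels V1 to V5. It states: "An intention-to-treat (ITT) analysis will be conducted, including all randomized patients in the analysis according to their assigned groups". Missing data are to be handled by multiple imputation or LOCF. Section 3 describes the main contrast as pre- against post-intervention values between arms. The sample size allows for 30% dropout among patients "who may experience side effects or other factors leading to withdrawal from the study".

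**The concern.** An ITT comparison at a visit label assumes that the label means the same elapsed time since randomization in both arms. Here the label depends partly on how much treatment the patient took. A patient who stops sessions early has no completion for V3 to mark, and that patient's end-of-NBO date comes sooner, so V4 and V5 come sooner too. A patient whose sessions are made up late would be seen later.

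Two things are at stake. The first is lost data: a post-test that could have been collected from a patient still in the study may go uncollected and be imputed. The second is comparability: blood counts, cytokines and stress markers may change over the course of chemotherapy, so mixing elapsed times under one label adds noise. If one arm stops or delays more than the other, it also adds a systematic difference.

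**Working it through.** **Inputs.** Ten sessions; two per week (section 2.6) or two blocks of five sessions over five weeks each (section 2.7, Table 1); V4 and V5 at 3 and 6 months after NBO (section 2.7); 127 per group and 30% dropout (section 2.10). Assumptions: 3 months = 13 weeks, 6 months = 26 weeks, first session in week 1, sessions evenly spread.

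**The plan's own calendar at full attendance.**
- Section 2.6: 10 sessions / 2 per week = 5 weeks. V3 is at week 5, V4 at 5 + 13 = 18, V5 at 5 + 26 = 31.
- Section 2.7 and Table 1: 5 + 5 = 10 weeks. V2 is at week 5, V3 at week 10, V4 at 10 + 13 = 23, V5 at 10 + 26 = 36.

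The two sections therefore differ by 5 weeks for V3, V4 and V5 before anyone misses a session.

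**Early stopping.** With L the week of the last session received, V4 = L + 13 and V5 = L + 26. Shift against a completer = (L of completer) − (L of stopper). The 13 and 26 cancel, so the shift does not depend on how months are converted to weeks.

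Example: last session is number 3.

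| Schedule | Completer: L, V4, V5 | Stopper: L, V4, V5 | Shift |
|---|---|---|---|
| One per week (2.7) | 10, 23, 36 | 3, 16, 29 | 7 weeks |
| Two per week (2.6), counted by calendar week | 5, 18, 31 | 2, 15, 28 | 3 weeks |
| Two per week (2.6), evenly spaced | 5, 18, 31 | 1.5, 14.5, 27.5 | 3.5 weeks |

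**Range over all early stops (last session 1 to 9).** One per week: shift = 10 − s, so 9 down to 1 week. Two per week, evenly spaced: shift = 5 − s/2, so 4.5 down to 0.5 weeks.

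**How many patients.** No figure is given for patients who stop sessions but stay in follow-up. The only related number is study dropout: 0.30 × 127 = 38.1, about 38 per arm. It is an upper bound, reached only if every planned dropout were instead such a patient. Someone who leaves the study supplies no V4 or V5 under any anchor.

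**The case against.** **The anchor is a natural one, and the calendar is not wholly missing.** V4 and V5 are meant to show long-term effects, and time since last exposure is a sensible clock for that. V2 and V3 can be placed at weeks 5 and 10 from the block lengths, and no sentence says that an early stopper is not assessed. This stands for V2 and softens the point for V3. It does not help V4 and V5, whose only stated reference is the end of NBO, and section 2.6 contradicts the block lengths.

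**The article is condensed.** Make-up sessions, visit windows and visits after early stopping commonly sit in the full protocol. That stands: their absence is not the point here. The point is the anchor that the article does state.

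**Stronger readings that a reader might infer, and why they fail.**
- *The post-test compares completers only.* Section 2.10 keeps all randomized patients as assigned, with imputation or LOCF; the completer-type analysis is the secondary per-protocol one. The cost is more imputed post-tests than necessary.
- *About 38 patients per arm are affected.* That figure is study dropout, as explained above.
- *Infection or bleeding will postpone sessions.* Section 2.4 lists these as contraindications among the entry exclusions. The article gives no postponement rule for them.
- *The arms will be sampled at different cumulative chemotherapy.* Both arms follow the same session course under the same anchor, so this needs stopping or delay to differ by arm. Sections 2.6.1 and 2.6.2 give the arms different pressure and carbon dioxide levels, so a difference in tolerance is conceivable, but no figure shows one. Nor is NBO tied to chemotherapy cycles. Dating visits from V1 would not align cycles patient by patient; it would keep the balance that randomization gives in expectation.

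**Conclusion.** The point holds in a limited form. V3 is tied to finishing the course, and V4 and V5 to the end of NBO, while the analysis is ITT by visit label. For a patient who stops sessions early and stays in the study, V3 is unclear, and V4 and V5 fall early by 1 to 9 weeks on the section 2.7 schedule or 0.5 to 4.5 weeks on the section 2.6 schedule. This rests on reading the end of NBO as the patient's own last session and on evenly spread sessions.

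The consequence in both arms is added timing variability and avoidable missing post-tests. Bias between arms is possible but conditional on differential stopping or delay, which the documents neither show nor exclude. This is a worthwhile, inexpensive improvement, not a flaw that invalidates the design.

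**What to change.** 1. Reconcile the course length in section 2.6 with that in section 2.7 and Table 1. The visit calendar cannot be written until this is done.
2. In section 2.7 and Table 1, give V2, V3, V4 and V5 as fixed weeks from V1, based on the planned course, each with a window.
3. State that these visits are held on those dates for every patient still in the study, whatever number of sessions was received.
4. Record the number of sessions received and the date of the last one, so that time since last exposure can still be examined.

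The cost is wording before the first enrollment, planned for March 2026, plus two recorded items; no visits are added. There is one small downside: where sessions are postponed, V3 may come before the patient's last session.

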### 2.3. Study Participants

The primary study population includes adult patients diagnosed with CRC (ICD10: C18–C20) undergoing chemotherapy. CRC patients commonly experience anemia, immune suppression, and oxidative stress as side effects of chemotherapy, which this study aims to address with NBO therapy. The selected study population is highly relevant due to the significant challenges CRC patients face during chemotherapy, including anemia, oxidative stress, and immune suppression, which impact both treatment outcomes and quality of life. NBO therapy holds potential as a supportive treatment to mitigate these adverse effects.

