### 2.4. Eligibility Criteria

Inclusion criteria: (1) age between 18 and 80 years (participants must be adults); (2) diagnosed with CRC (stage II–IV, scheduled for standard chemotherapy (for the study and control groups); (3) baseline hemoglobin levels above 10 g/dL; (4) no concurrent hematologic malignancies; (5) an eastern Cooperative Oncology Group (ECOG) performance status of 0–2 (ensuring that participants are ambulatory and capable of self-care); (6) a life expectancy of at least 12 months (participants are expected to survive for the duration of the study); (7) the ability and a willingness to comply with all study procedures and schedules (including NBO therapy sessions and follow-up visits); (8) adequate organ function as determined by laboratory tests (liver function tests (ALT, AST) and renal function tests (serum creatinine, eGFR)); (9) women of childbearing potential must have had a negative pregnancy test prior to enrollment and agreed to use effective contraception during the study (to ensure safety for potential pregnancies); and (10) written informed consent was obtained prior to any study-related procedures (participants must understand and agree to all aspects of the study).

Exclusion criteria: (1) age under 18 years or over 80 years; (2) severe cardiovascular or respiratory conditions (e.g., unstable angina, recent myocardial infarction, advanced COPD); (3) severe anemia (hemoglobin < 10 g/dL) or any hemolytic disorder that could confound study outcomes; (4) uncontrolled diabetes mellitus (e.g., HbA1c > 8.0% or poor glycemic control requiring frequent hospitalizations); (5) pregnancy or breastfeeding; (6) severe infection or immunocompromised status unrelated to cancer (e.g., advanced HIV infection); (7) current psychiatric or neurological disorders that could interfere with study participation; (8) participation in other investigational therapies within the last 30 days; (9) a lack of written informed consent for study participation; (10) autoimmune or inflammatory conditions (e.g., lupus, rheumatoid arthritis on immunosuppressive therapy) that significantly alter immune responses; and (11) the presence of any contraindication for NBO therapy (e.g., active bleeding, acute infections, inflammation of the optic nerve, epilepsy or seizures, uncontrolled diabetes as noted above, pneumothorax, emphysema, electronic implants).

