### 2.10. Statistical Analysis

Descriptive statistics will be used to summarize study results. Central tendency and dispersion measures will be calculated using parametric or non-parametric methods depending on data distributions. Repeated measures data (V1, V2, V3, V4, and V5) will include ordinal and interval data analyzed with repeated measures ANOVA (parametric) or the Friedman test (non-parametric). Data normality will be verified with the Shapiro–Wilk test. Depending on the distribution, data will be presented as means with standard deviations (parametric) or medians with interquartile ranges (IQRs) (non-parametric). Comparisons between baseline (V1) and follow-up (V4, V5) visits will use the Wilcoxon signed-rank test for paired variables and the Friedman test for multiple comparisons. Post hoc analysis (for significant Friedman tests) will apply Wilcoxon tests with Bonferroni corrections. For between-group comparisons (intervention vs. control), the Mann–Whitney U test will be used.

A comprehensive sample size analysis was conducted to ensure that the study is adequately powered to detect a statistically significant effect of NBO therapy on erythropoiesis stimulation among patients undergoing chemotherapy. The primary endpoint considered was the assumed 40% difference between the active NBO group and the placebo group in the primary outcome measure related to erythropoiesis, such as erythropoietin (EPO) levels. To achieve adequate statistical power, the analysis aimed for 80% power (β = 0.20), indicating a high probability of detecting a true effect if it exists, at a significance level of 5% (α = 0.05), which is the conventional threshold for statistical significance. Effect size estimation was based on Cohen’s (1992) [41] classification, where a small effect size ranges from 0.1 to 0.29, a medium effect size ranges from 0.3 to 0.49, and a large effect size ranges from 0.5 to 1. An effect size corresponding to a medium to large effect was anticipated due to the expected impact of NBO on erythropoiesis.

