## Figures and Tables

**Figure 1 jcm-14-05057-f001:**
[figure not shown]
Flow diagram of the study course.

**Table 1 jcm-14-05057-t001:** Research plan.

Visit	Phase	Assessments
V0	Prequalification (screening)	Consent, patient history, baseline data
V1	Randomization and pre-test	ANEMIA, STRESS, IMMUNE, GENETIC, PROMs + BIOBANK
NBO sessions 1–5		NBO intervention (first five weeks)
V2	Midpoint evaluation	ANEMIA, STRESS, IMMUNE, GENETIC, PROMs
NBO sessions 6–10		NBO intervention (second five weeks)
V3	Finalization and post-test	ANEMIA, STRESS, IMMUNE, GENETIC, PROMs
V4	3 month follow-up	ANEMIA, STRESS, IMMUNE, GENETIC, PROMs
V5	6 month follow-up	ANEMIA, STRESS, IMMUNE, GENETIC, PROMs

Abbreviations: NBO, normobaric oxygen intervention; V, visit; I, Intervention; ANEMIA, assessment of erythropoiesis markers; STRESS, assessment of stress and oxidative stress; IMMUNO, immunological parameter assessment; GENETIC, analysis of the secretome and molecular changes; PROMs, patient-reported measure outcomes; BIOBANK, collection of human biological material (blood samples) in accordance with the Quality Standards for Polish Biobanks v. 2.00 (2021).

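### No visit is tied to chemotherapy, so the planned within-arm V1-to-V4/V5 tests cannot show a long-term NBO effect, and chemotherapy phase at sampling can add avoidable noise

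*Protocol article*

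**What the plan says.** All references are to the protocol article.

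- **Visit schedule (Section 2.7, Table 1).** "V1 (randomization and pre-test visit) will involve the initial assessments", before the first NBO session. V2 follows sessions 1–5: "the first phase of the NBO intervention (sessions 1–5) will take place over five weeks". "V3 (finalization and post-test visit) will mark the completion of the intervention". The follow-up visits are "V4 (3 months post-NBO) and V5 (6 months post-NBO", and Section 2.7 says they serve to evaluate the intervention's long-term effects.
- **Entry.** Section 2.3 describes the population as "adult patients diagnosed with CRC (ICD10: C18–C20) undergoing chemotherapy". The inclusion criterion in Section 2.4 reads "scheduled for standard chemotherapy (for the study and control groups". Neither limits the cycle number or the time since chemotherapy started.
- **Stratification (Section 2.5).** CRC stage (II, III, IV) and baseline hemoglobin (below 12 g/dL or not).
- **Analysis (Section 2.10).** "Comparisons between baseline (V1) and follow-up (V4, V5) visits will use the Wilcoxon signed-rank test for paired variables". Between-group comparisons use the Mann–Whitney U test, with no covariates named.
- **Role of chemotherapy.** The Introduction attributes the anemia largely to myelosuppression by cytotoxic agents. Sections 2.3 and 4 link chemotherapy to anemia, oxidative stress and immune suppression, which are the primary outcome domains.

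**The concern.** The protocol names chemotherapy as a driver of its own primary outcomes but leaves chemotherapy exposure open at every measurement. On the text as it stands, one patient could give the V1 sample before any cytotoxic dose and another after several cycles. At V4 or V5 one patient could still be on treatment and another recovering after its end.

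Two things are at stake. First, a paired change from V1 to V4 or V5 within one arm mixes any NBO effect with the effect of starting or stopping chemotherapy, so it cannot carry the long-term claim made for those visits. Second, if samples fall at different chemotherapy phases, outcomes that respond to chemotherapy vary more between patients than they need to, and the between-arm test loses power.

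**Working it through.** **Step 1. Anchor of each visit (Section 2.7, Table 1).**

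| Visit | Anchor stated | Anchor to chemotherapy |
|---|---|---|
| V1 | randomization, before NBO session 1 | none |
| V2 | after sessions 1–5 | none |
| V3 | completion of sessions 6–10 | none |
| V4 | 3 months after NBO | none |
| V5 | 6 months after NBO | none |

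The start of NBO is not tied to chemotherapy either, so the visits cannot be placed indirectly.

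**Step 2. Calendar position of the visits.** Section 2.6 puts the ten sessions in five weeks; Section 2.7 and Table 1 give five weeks plus five weeks, which is ten. Counting 3 months as 13 weeks and 6 months as 26 weeks from the start of NBO:

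- Five-week course: V3 at week 5, V4 at 5 + 13 = 18, V5 at 5 + 26 = 31.
- Ten-week course: V3 at week 10, V4 at 10 + 13 = 23, V5 at 10 + 26 = 36.

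This separate contradiction makes the later visits harder still to place; those passages must be reconciled.

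**Step 3. What each planned contrast can show.** Let C be the change that chemotherapy causes in a marker between V1 and a later visit, and N the change that active NBO causes. Treat the two as additive for simplicity.

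- Within the active arm, V1 to V5 estimates C + N. Within the placebo arm it estimates C. A significant paired test in the active arm is compatible with N = 0.
- Between arms, the difference is (C + N) − C = N, because randomization gives both arms the same C on average.

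Only the between-arm contrast isolates NBO.

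**Step 4. Illustration of the cost in power.** Section 2.10 gives 127 per group, 30% dropout, two-sided α = 0.05, 80% power, 1:1 allocation and a t-test of two means. It states no numerical d or SD, so 127 cannot be derived from the stated inputs alone. Working back:

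- Evaluable per arm: 127 × 0.70 = 88.9, about 89.
- d giving 80% power with 89 per arm (exact t-test): 0.422.

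As a check, d = 0.42 needs 90 per arm, and 90 / 0.70 = 129, close to 127. The figure can also be approached with d = 0.40 and multiplication by 1.3 (100 × 1.3 = 130), so d = 0.42 is one possible reading.

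If chemotherapy phase adds a proportion v to the outcome variance, the effective effect size is 0.422 / √(1 + v). The range of v is assumed.

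| v | Effective d | Power, 89 per arm | Evaluable per arm for 80% |
|---|---|---|---|
| 0 | 0.422 | 80% | 89 |
| 0.10 | 0.403 | 76% | 98 |
| 0.25 | 0.378 | 71% | 112 |
| 0.50 | 0.345 | 63% | 134 |
| 1.00 | 0.299 | 51% | 178 |

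**The case against.** **Randomization already deals with this.** The trial is randomized 1:1 against placebo, Section 2.6.2 gives the placebo arm the task of separating NBO from the natural course of treatment, and Section 3 compares pre- and post-intervention values between arms. This stands. A reader might infer that the unanchored schedule biases the active-versus-placebo comparison, or makes V4 and V5 uninterpretable altogether. The document does not support that: recovery after chemotherapy is expected equally in both arms.

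**The entry wordings are compatible.** Patients scheduled for chemotherapy at entry may be undergoing it during the intervention. This is a fair reading, so the two sections are not a plain contradiction, and a mix of pre-, on- and post-chemotherapy states is something the text permits rather than states. Even on that reading, nothing places V1 or session 1 relative to the first cycle.

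**Stage is a stratification factor.** To the extent that treatment duration depends on stage, stratification covers part of the on/off difference at V4 and V5. It would be too strong to say that it captures none of it.

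**The article is condensed.** Sampling windows and case report form fields may well sit in the full protocol, and their absence here is not held against the plan. The visit anchors, the paired tests and the long-term reading of V4 and V5 are stated text.

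**The power figures prove nothing.** They rest on a back-solved d and an assumed v. Section 2.10 takes the SD from pilot studies or the literature; if those samples were already mixed in phase, the extra variance is already counted. The document also gives no ground for extending the noise argument to every listed marker. This stands, and the table in the working is only an illustration.

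**Within-arm tests are weak whatever the timing.** True: fixing visit timing alone would not rescue them. That is why the analysis change comes first in the fix.

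**Conclusion.** The point holds in a limited form. V1 is tied to randomization and V2–V5 to the NBO course, none to chemotherapy, and the entry wording does not close the gap.

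- **Firm, with no numerical assumption:** the within-arm V1-to-V4 and V1-to-V5 Wilcoxon tests cannot establish a long-term effect of NBO, since starting or stopping chemotherapy may produce the same change.
- **Plausible, size unknown:** chemotherapy phase at sampling can add avoidable variance to blood counts and other chemotherapy-sensitive outcomes. The fall in power to between 76% and 51% is conditional on d = 0.42 and 10% to 100% added variance. It is not an estimate for this trial.
- **Not supported:** bias in the active-versus-placebo contrast, at V3 or at V4 and V5.

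This should be corrected before the first enrolment, planned for March 2026, because exposure timing that is not captured prospectively may be hard to recover.

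**What to change.** 1. **Analysis (Section 2.10).** Make the between-arm contrast, adjusted for the V1 value and the stratification factors, the test of the objectives at V3 and of long-term effect at V4 and V5. Label the within-arm paired tests as descriptive only.
2. **Entry and sampling (Sections 2.3, 2.4, 2.7).** Reconcile the two entry wordings so that the position of V1 relative to chemotherapy is clear. Take V1–V3 study blood at one stated cycle phase, for example the routine pre-dose sample nearest the planned visit.
3. **Data.** Record cycle number, days since last dose and on/off chemotherapy status at every visit. Use chemotherapy status at V1, which precedes the intervention, as a covariate.
4. **What to avoid.** Do not split V4 and V5 by on/off chemotherapy as a main analysis. That status arises after randomization and could itself be affected by NBO through tolerability, so the split could bias a comparison that randomization now protects. Show it descriptively only.

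**Cost.** A few days of visit-window flexibility, a few extra data fields and revised wording. Patients already part-way through chemotherapy need not be excluded, provided their cycle number and status at V1 are recorded. The sample size need not change on this account.
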